#### Randomisation and Treatment

This will be a double-blind randomised comparison. The randomization code will be computer generated and will be made for blocks of 40 cases. The study drugs will be presented in sealed plastic bottles; each bottle will contain sufficient tablets to complete one course of treatment (10 tablets, 150mg chloroquine base per tablet). Once the bottle is opened the patient will be considered to have entered the trial whatever happens subsequently. Patients will be randomized to group A or group B.

Group A: Chloroquine: 600mg base (4 tablets) on admission to the study, then 600mg 24hrs later (day 2), then 300mg on day 3.

GroupB: Placebo. Same regime of tablets (identically sized) as per chloroquine arm

#### Observations and Investigations

A full history and clinical examination will be performed at study entry and every day during the inpatient period. All clinical data will be documented in the case record form. The following investigations will be performed;

1. Chest X-ray or ultrasound on day of defervescance.
2. Hct, white cell count/differential, platelet count, SGOT, SGPT daily
3. Twice daily viral culture from plasma for minimum 5 days
4. Twice daily quantitative viral PCR from plasma for minimum 5 days
5. Twice daily assessment of Dengue NS1 levels for minimum 5 days
6. Twice daily measurement of plasma concentrations of the pro-inflammatory cytokines TNF, IL-6, IL-1B, IL12, IL-8 and the anti-inflammatory, IL-10 for minimum 5 days
7. ELISPOT assays to quantitate DENV-specific T cell responses
8. Microarray and PCR investigations to measure the effect of chloroquine on host gene-expression responses during acute disease

**Trial monitoring and Adverse events**

There will not be an interim analysis of the trial because of the relatively small sample size. All serious adverse events will be reported to the independent data safety and monitoring committee (DSMC). All adverse events will be recorded in the adverse events form found in the case record forms.

**Blood sample collection**

Venous blood (2ml) will be collected from all cases twice daily for a minimum of 5 days after starting treatment. This 2ml sample is sufficient to evaluate viral and haematological parameters. At the time of discharge, a 5ml blood sample will be collected to measure dengue-specific T cell responses.

**Vomiting protocol**

In the event the patient vomits within 5 minutes of receiving the study drug, then the patient will be re-dosed.

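### The sealed bottle holds no spare tablets for the re-dosing that the vomiting rule requires, and the protocol describes no other allocation-matched source

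*Protocol*

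**What the plan says.** The Protocol's Randomisation and Treatment section fixes both supply and course. On supply: "each bottle will contain sufficient tablets to complete one course of treatment (10 tablets, 150mg chloroquine base per tablet"). On the active course: "600mg base (4 tablets) on admission to the study, then 600mg 24hrs later (day 2), then 300mg on day 3". The placebo arm mirrors it: "Same regime of tablets (identically sized) as per chloroquine arm". The same section declares the design: "This will be a double-blind randomised comparison".

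The Vomiting protocol section is a single sentence: "In the event the patient vomits within 5 minutes of receiving the study drug, then the patient will be re-dosed". It does not say how much is repeated, how often, or where the tablets come from. The protocol mentions no overage, spare bottle or replacement supply.

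**The concern.** A stated pack content and a stated rule do not fit together. The bottle is sized for a course in which no dose is repeated, while the vomiting rule is unconditional. With the supply described, a patient who is re-dosed cannot receive both the repeat and the rest of the course.

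The statistical interest lies in how a ward might cope. The only other study tablets described are in other sealed bottles, and blinded staff cannot tell which arm those hold. Tablets from such a bottle could give active drug to a placebo patient, or placebo to a chloroquine patient. That would blur the contrast on NS1 and PCR clearance, and it would disturb the allocation sequence if the bottle was meant for someone else. The patients concerned are picked out by an event after randomisation, early vomiting, whose frequency could differ between arms, although the protocol gives no data on this.

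**Working it through.** **Inputs.** From Randomisation and Treatment: 10 tablets of 150 mg base per bottle; doses of 600, 600 and 300 mg; blocks of 40. From Sample Size: 110 patients per arm, 220 in all. Assumptions not in the document: the vomited dose is repeated in full, and each block of 40 is split 20:20.

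**The plan's own figure.** Tablets per course = (600 + 600 + 300) / 150 = 4 + 4 + 2 = 10, and 10 × 150 = 1500 mg. The stated bottle content is reproduced exactly, with 0 tablets to spare.

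**One full repeat, by day.**

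| Dose vomited | Left in bottle after that dose | Repeat needs | Still due later | Shortfall |
|---|---|---|---|---|
| Day 1 | 10 − 4 = 6 | 4 | 6 | 4 + 6 − 6 = 4 |
| Day 2 | 10 − 8 = 2 | 4 | 2 | 4 + 2 − 2 = 4 |
| Day 3 | 10 − 10 = 0 | 2 | 0 | 2 + 0 − 0 = 2 |

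The shortfall is 4/10 = 40% of the bottle on day 1 or 2, and 2/10 = 20% on day 3. On day 1 the repeat can be given from the patient's own bottle, but only 2 tablets then remain against 6 due. On day 2 or 3 a full repeat cannot be given from that bottle at all. If more than one dose is repeated, the need rises to between 16 tablets (day 3 and one earlier dose) and 20 tablets (all three), a shortfall of 6 to 10.

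**If another bottle were used.** In a block of 40 split 20:20, setting aside the patient's own bottle leaves 39, of which 20 hold the other arm: 20/39 = 0.513, about 51%.

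**How many patients.** The protocol gives no rate of vomiting within 5 minutes. Each percentage point of the 220 patients is 0.01 × 220 = 2.2 patients. Purely as an illustration, a rate of 5% to 10% would mean 11 to 22 re-dosed patients. If every one of them were re-dosed from a randomly chosen bottle in the same block, 11 × 0.513 = 5.6 to 22 × 0.513 = 11.3 would receive tablets of the other arm, or 2.6% to 5.1% of 220. The 5-minute window is narrow, so the true rate may well lie below this range.

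**The case against.** **The two sections do not strictly contradict each other.** One describes a bottle and the other a re-dose, and neither says that the bottles are the only supply. This stands to a degree. A reader might infer that a re-dosed patient is bound to receive tablets of unknown allocation or go short. The document does not support that, because a reserve matched to the patient's allocation is neither described nor excluded. What survives is narrower: the stated content, called sufficient for a course, cannot serve the stated rule, and no other source is named.

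**Trial entry.** The protocol says: "Once the bottle is opened the patient will be considered to have entered the trial whatever happens subsequently". A reader might infer that opening a second bottle for a re-dose creates a further trial entry. It does not. The sentence defines when a patient enters, and a patient being re-dosed has already entered. A randomisation slot would be lost only if a bottle intended for another patient were opened, and nothing in the protocol tells staff to do that.

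**The vomiting, not the re-dose, loses the drug.** If the day 1 dose is wholly lost, 6 tablets remain to be retained whether or not a repeat is given. This is correct: re-dosing from the patient's own bottle only moves tablets earlier and does not reduce the total retained. It also shows that, with this pack, the rule cannot make good the lost dose.

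**The effect on the result is not shown.** This also stands. The full repeat, the 20:20 split and any vomiting rate are assumptions. Most affected patients would probably be exposed for one dose only. The primary analysis is further limited to patients who are NS1 or PCR positive at entry, and the trial is planned around a hazard ratio of 2. A few partly mixed exposures are not shown to threaten that comparison.

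**Conclusion.** The point holds as a minor one. The tablet count is exact and rests on the protocol alone: 10 supplied, 10 used, none spare, against an unconditional re-dosing rule. The shortfall of 2 or 4 tablets per re-dose assumes that the vomited dose is repeated in full. The 51% chance of the other arm assumes 20:20 balance within a block and applies only if staff turn to another bottle, which the protocol neither directs nor forbids. The number of patients affected cannot be derived from the document and is probably small. No sample-size or error-rate figure changes. It is still worth correcting before the start, because staff in a double-blind trial cannot safely improvise a source of tablets.

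**What to change.** Reconcile Randomisation and Treatment with Vomiting protocol in two steps:

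- Change the stated pack content so that it includes reserve tablets of the patient's own allocation, packed under the same randomisation number and identical in number in both arms. If such a reserve is already planned, describing it is enough.
- State that tablets for a repeat dose are never taken from another patient's bottle.

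The size of the reserve follows from the rule that the investigators settle. On the present regimen, one full repeat of any single dose would use up to 4 extra tablets, and one full repeat of all three would use 10. This concerns supply and allocation only; whether, how much and how often to re-dose is for the investigators.

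The cost is a change to packing and labels, a sentence or two in the protocol, and a few extra tablets per pack.

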# **Analysis plan- primary endpoints**

Baseline variables at randomization will be compared between the 2 treatment groups and analysed using the Kruskal-Wallis test for continuous variables and the chi-square test (or Fisher’s exact test) for categorical variables. Only study subjects who have detectable NS1 antigenaemia or viraemia (detected by PCR) at the time of study entry will be analysed for the primary endpoint measures. The primary endpoints are time to negative DENV NS1 antigenaemia in plasma and time to negative reverse transcriptase (RT)-PCR detection of viral RNA in plasma. Comparison of Kaplan-Meier survival curves (representing proportion of cases NS1 or PCR positive) between treatment groups using log-rank test will be performed. Adjusted treatment effect will be estimated and independent predictors will be identified using Cox regression analysis with stepwise forward variable selection procedure.

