**Study Aims**

To measure the antiviral efficacy of chloroquine in the treatment of dengue.

Primary endpoint

The primary endpoint is;

1. time to negative DENV NS1 antigenaemia in plasma
2. time to negative reverse transcriptase (RT)-PCR detection of viral RNA in plasma

For the purposes of the study, time to a negative NS1 or PCR will be the interval between starting treatment and the first time NS1 or PCR is negative and remains negative for two consecutive measurements.

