#### Sample Size

The following assumptions were made in calculating the sample size for EF study:

1. The median time to NS1 and PCR clearance in dengue population with normal standard of care is 72 hours
2. Most (90%) of dengue patients admitted to the trial will be day 3 of illness
3. The average proportion of cases that are NS1 and/or PCR positive on day 3 is 80%
4. At the end of follow-up (5 days after study entry), 20% of cases will still be positive for NS1
5. 10% of patients lost to follow-up

Under these assumptions, the minimum number of NS1 or PCR clearance cases required to be able to detect a 36 hours reduction of median time in Chloroquine arm as compared to standard care arm with a power of 0.8 and type I error 0.05--equivalently a hazard ratio relating to NS1 clearance of 2—is 72. Therefore total number will be 138/{0.8*(1-0.1)*(1-0.1)} =220 or 110 patients in each arm. The effect size in this sample size calculation study is large, but can be justified on the basis that a smaller effect size is unlikely to be clinically significant.

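### The entry condition for the primary analyses does not require positivity on the marker being analysed; read literally, it dilutes each clearance comparison

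*Protocol*

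**What the plan says.** The Protocol's section on the analysis of primary endpoints sets one condition for entering the primary analyses: "Only study subjects who have detectable NS1 antigenaemia or viraemia (detected by PCR) at the time of study entry will be analysed". It then names two distinct outcomes: "The primary endpoints are time to negative DENV NS1 antigenaemia in plasma and time to negative reverse transcriptase (RT)-PCR detection of viral RNA in plasma". The comparison is by log-rank test: "Comparison of Kaplan-Meier survival curves (representing proportion of cases NS1 or PCR positive) between treatment groups using log-rank test will be performed".

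Under Study Aims, the clock runs from the start of treatment to "the first time NS1 or PCR is negative and remains negative for two consecutive measurements". No rule is given for a patient who is already negative on that marker when treatment starts.

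The Sample Size section plans with one positivity figure for both markers: "The average proportion of cases that are NS1 and/or PCR positive on day 3 is 80" per cent.

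**The concern.** The condition joins the markers with *or*, while the endpoints are analysed one marker at a time. A patient who is PCR-positive and NS1-negative at entry satisfies it and so belongs to the NS1 analysis as well. If the next sample is also NS1-negative, the definition is met at the first measurement, and NS1 clearance falls at or near time zero, before any drug effect is possible. The same applies in reverse for PCR.

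Such events are expected in equal proportion in both arms. They add events and variance but no treatment information, so the hazard ratio moves toward 1 and both medians shorten. The estimate is affected as well as the power: the Sample Size section argues that an effect smaller than a hazard ratio of 2 is unlikely to matter clinically, so a diluted estimate could be dismissed on the protocol's own standard. The 80% figure has a related weakness. If it describes patients positive on at least one marker, the number positive on each single marker can only be equal or lower.

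**Working it through.** **Inputs from the protocol.** Control median 72 h; reduction of 36 h, so 36 h on chloroquine; hazard ratio for clearance 2; "power of 0.8 and type I error 0.05"; follow-up 5 days (120 h); twice-daily sampling, taken as 12-hourly; 220 patients, 1:1; divisor 0.8 × 0.9 × 0.9.

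**Assumed.** Exponential clearance, and the share f of the either-marker set already negative on the analysed marker. The documents give no value for f, so 10% to 40% is shown.

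**1. The plan's own figure.** Freedman's formula, two-sided: events = (1.960 + 0.842)² × [(2 + 1)/(2 − 1)]² = 7.85 × 9 = 70.6, so 71. This agrees with the stated 72 within rounding. (Schoenfeld's formula gives 66.)

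**2. Size of the analysis set.** 220 × 0.8 × 0.9 × 0.9 = 142.6, about 71 per arm. By 120 h the share cleared is 1 − 2^(−120/72) = 0.685 on control and 1 − 2^(−120/36) = 0.901 on chloroquine, giving 71 × (0.685 + 0.901) = 112.6 events when f = 0. The average, 79%, fits the protocol's assumption that 20% remain positive.

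**3. Medians.** With a share f cleared at time zero, the proportion still positive is (1 − f) × 2^(−t/M). Setting this to 0.5 gives t = M × [1 + log2(1 − f)]. At f = 20%: 72 × 0.678 = 48.8 h and 36 × 0.678 = 24.4 h, a difference of 24.4 h instead of 36 h.

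**4. Hand check of the dilution at f = 20%.** Time-zero events: 0.2 × 142 = 28.4. Their log-rank variance is 28.4 × 0.25 × (142 − 28.4)/(142 − 1) = 5.7, with no expected treatment difference. The remaining events, 112.6 × 0.8 = 90, carry a variance of about 90 × 0.25 = 22.5. The log hazard ratio shrinks by 22.5/(22.5 + 5.7) = 0.80, so ln 2 × 0.80 = 0.553, a hazard ratio of 1.74. The expected test statistic is 0.693 × 22.5/√28.2 = 2.94 as written and 0.693 × √22.5 = 3.29 if restricted, giving power of about 0.84 and 0.91.

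**5. Simulation.** 71 per arm, medians 72 h and 36 h, 12-hourly sampling, censoring at 120 h, log-rank test, Cox model with Efron ties, 1,500 trials per setting. Power is shown for two separate simulations; the other columns are from the first, except the median difference, which comes from step 3.

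| f | HR, as written | Power, as written | HR, restricted | Power, restricted | Events, restricted | Median difference, as written |
|---|---|---|---|---|---|---|
| 10% | 1.85 | 0.90, 0.90 | 2.00 | 0.94, 0.93 | 101 | 30.5 h |
| 20% | 1.69 | 0.83, 0.83 | 2.02 | 0.92, 0.90 | 90 | 24.4 h |
| 30% | 1.56 | 0.70, 0.71 | 2.01 | 0.87, 0.87 | 79 | 17.5 h |
| 40% | 1.46 | 0.61, 0.59 | 2.03 | 0.82, 0.81 | 67 | 9.5 h |

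At f = 0 power is about 0.95. Scoring these patients at the first 12 h sample instead of time zero gives nearly the same hazard ratios as written: 1.85, 1.71, 1.59 and 1.49.

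**6. At the bare event target.** The Sample Size section states 72 events but divides 138, a separate discrepancy. With 46 per arm (about 73 events at f = 0), power is about 0.85 at f = 0. As written it falls to 0.74, 0.62, 0.54 and 0.43; restricted, it is 0.80, 0.77, 0.69 and 0.64.

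**The case against.** **The sentence may be meant marker by marker.** The protocol uses the same shorthand for two separate endpoints elsewhere: "time to a negative NS1 or PCR will be the interval between starting treatment and the first time NS1 or PCR is negative", and again in describing the Kaplan-Meier curves. A curve of the proportion still positive suggests that everyone starts positive. The word *average* attached to the 80% could mean an average over the two markers. This reading is possible, and it limits confidence. But nothing in the text says that each condition belongs to its own endpoint, and *and/or* in the sample size assumption fits the either-marker set better.

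**Time zero is an inference.** No section says how a patient negative at entry is scored, and a statistical analysis plan that is not shown may settle it. If time-zero records were dropped, the hazard ratio would not be diluted, but the set analysed would then differ from the one written. This stands as a caveat. It does not excuse the sentence, because the protocol states the analysis set itself and does not leave it open.

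**The size depends on f.** At f = 20% with the full sample, power as written is still 0.83, above the planned 0.80, and at 10% the loss is small. This stands. A reader might infer that the trial is underpowered; at full size that needs f of about 30% or more, which no figure in the documents supports.

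**Later positivity.** A reader might also infer that anyone negative at entry is scored as cleared even if the marker appears later. The definition requires the marker to remain negative for two consecutive measurements, so a patient positive at the next sample is not cleared at entry. Only a return after the required negatives would be missed.

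**Conclusion.** The concern holds in a limited form. As worded, the entry condition lets patients already negative on a marker into that marker's time-to-negative analysis, and the definition of clearance then places their event at or near time zero. This applies to both primary endpoints. For f of 10% to 40% and a true hazard ratio of 2, the estimate falls to about 1.85 to 1.46 and power to about 0.90 to 0.6. Restriction keeps the hazard ratio near 2 and gives higher power at every f tested, despite fewer events.

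The result rests on the either-marker reading, on scoring these patients at or near time zero, on exponential clearance, and on a value of f that the protocol does not report. The bias is toward no difference, so the documents do not support reading this as a risk of a false positive result. Should be fixed; moderate confidence.

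**What to change.** Replace the condition in the analysis of primary endpoints with wording such as:

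> The NS1 endpoint is analysed in patients who are NS1-positive at study entry, and the PCR endpoint in patients who are PCR-positive at study entry. The study-entry sample is the one taken before the first dose of study drug.

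In the Sample Size section, replace the single 80% with the expected positivity for each marker and restate the power for each endpoint.

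**Cost.** Each endpoint has fewer patients and events: about 101 to 67 events for f of 10% to 40%, against about 113 if every patient in the set were positive on that marker. Patients who are negative on a marker at entry and become positive later leave that endpoint and can be described separately. The change appears to need no new measurements, since the plan already uses marker status at entry, and the Subgroup analysis section already uses viraemia and NS1 levels at the start of treatment. The sponsor should confirm that this sample precedes the first dose, because the Blood sample collection section describes sampling after starting treatment. Selecting on a value measured before the first dose keeps the randomised comparison intact.

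### Two primary endpoints share one stated type I error of 0.05 with no rule for combining them, so the 0.05 is not secured and a split result has no agreed reading

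*Protocol*

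**What the plan says.** Three sections of the protocol bear on this.

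- **Study Aims** opens in the singular, "The primary endpoint is", then lists two numbered items, NS1 clearance and RT-PCR clearance. One definition serves both: "time to a negative NS1 or PCR will be the interval between starting treatment and the first time NS1 or PCR is negative", with the negative result to be sustained over two consecutive measurements.
- **Analysis plan- primary endpoints** uses the plural: "The primary endpoints are time to negative DENV NS1 antigenaemia in plasma and time to negative reverse transcriptase (RT)-PCR detection of viral RNA". It prescribes a log-rank comparison of Kaplan-Meier curves for patients who remain positive, joining the two markers by *or*. It gives no split of the significance level, no order of testing and no success rule.
- **Sample Size** has one calculation, "with a power of 0.8 and type I error 0.05". It yields 72 as "the minimum number of NS1 or PCR clearance cases required to be able to detect a 36 hours reduction of median time". The effect is expressed as "a hazard ratio relating to NS1 clearance of 2", so the hazard ratio is tied to one of the two markers.

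The section on trial monitoring rules out an interim analysis, so interim looks add nothing to the multiplicity considered here.

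**The concern.** A single error rate of 0.05 and a single event count belong to one hypothesis test. The analysis section names two primary endpoints and, on its plainest reading, compares the arms on each. The protocol does not say how two p-values become one conclusion about antiviral efficacy.

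Two things are at stake. First, if either marker can carry the claim at 0.05, the chance of a false claim exceeds the stated rate. Second, antigen and RNA are separate measures, so one may be significant and the other not. With no rule fixed beforehand, the reading of that result would be chosen after seeing it. The rule also determines how many events are needed, and the protocol itself sets that number.

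**Working it through.** **Inputs.** From Sample Size: type I error 0.05, power 0.80, hazard ratio 2 (median 72 h against 36 h), 72 events, 220 patients in two equal arms, 80% positive at entry for NS1 and/or PCR, 20% still NS1-positive at the end of follow-up, and two factors of 0.9 in the inflation formula. Sidedness is not stated; two-sided is assumed. The correlation between the two log-rank statistics is not given, so a range is shown.

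**1. The protocol's own figure.** For one two-sided test at 0.05 with 80% power, (1.960 + 0.842)² = 7.85.
- Freedman: 7.85 × [(2+1)/(2−1)]² = 7.85 × 9 = 70.6, so 71 events.
- Schoenfeld: 4 × 7.85 / (ln 2)² = 65.4, so 66 events.

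The stated 72 agrees with Freedman. One-sided 0.05 would give 52 (Schoenfeld) or 56 (Freedman) and does not match. The 72 therefore rests on one test at the full two-sided 0.05.

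**2. Error rate if either marker suffices at 0.05.** For independent tests it is 1 − 0.95² = 0.0975. For correlated statistics it is 1 − P(|Z₁|<1.96 and |Z₂|<1.96) under a bivariate normal distribution:

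| Correlation | 0 | 0.3 | 0.5 | 0.7 | 0.9 | 0.95 | 1 |
|---|---|---|---|---|---|---|---|
| Chance of at least one p<0.05 | 9.75% | 9.5% | 9.1% | 8.3% | 7.0% | 6.5% | 5% |

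**3. If both markers must be significant.** The error rate is at most 0.05. With 72 events on each marker, the power to win both is 0.70 at correlation 0 and 0.79 at 0.9 (Schoenfeld), below the stated 0.80.

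**4. Events needed at 0.025.** (2.241 + 0.842)² = 9.50. Freedman: 9.50 × 9 = 85.5, so 86. Schoenfeld: 4 × 9.50 / 0.480 = 79.1, so 80.

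**5. Power at 0.025, hazard ratio 2.** The Schoenfeld figure is Φ(√(E/4)·ln 2 − 2.241) and the Freedman figure is Φ(√E/3 − 2.241), where E is the number of events.

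| Events on a marker | Source | Freedman | Schoenfeld |
|---|---|---|---|
| 72 | stated in the protocol | 72% | 76% |
| 86 | 220 × 0.6 × 0.9 × 0.9 × 0.8, if 60% are positive on that marker (assumption) | 80% | 83% |
| 114 | 220 × 0.8 × 0.9 × 0.9 × 0.8 | 91% | 93% |
| 127 | 220 × 0.8 × 0.9 × 0.8 | 93% | 95% |

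The last two rows apply to each single marker an 80% that is stated for NS1 and/or PCR together, and to PCR a 20% residual that is stated for NS1 only. They are ceilings, not per-marker figures from the protocol.

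**6. Power of a first test at the full 0.05.** With 72 events it is Φ(√72/3 − 1.960) = 81% (Freedman) or 84% (Schoenfeld).

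**The case against.** **A reader might infer that the protocol lets either marker win, and hence that 0.05 is definitely breached.** The text does not say so. If both markers were required, or if one were tested first, 0.05 would hold without adjustment. The or-wording in the Kaplan-Meier sentence and in the event count could also describe one composite curve, which would mean one test and no inflation. The numbered list in Study Aims and the plural in the analysis section favour two endpoints, but do not settle it. This part of the objection stands: the defect is an unstated rule, and the inflation is conditional on one reading of it.

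**The markers are probably positively correlated.** They are measured in the same patients at the same twice-daily samples. This too stands. The 9.75% is the independence figure, the top of the range shown, and nothing in the documents fixes where in the range the trial would fall.

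**A reader might infer that 91-95% power at 0.025 follows from the protocol's assumptions, so that correction is nearly free.** It does not follow, because the protocol gives no positivity rate for either marker alone and no residual for PCR.

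**The rule may be in a statistical analysis plan that is not shown.** Such a plan may indeed hold it. But this protocol has its own primary analysis section and fixes the error rate and the event count. Those statements do not fit together until a rule is given, so the point concerns what is written and not only missing detail.

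**Conclusion.** The point holds in conditional form. The protocol states one error rate and an event count for one test, but names two primary endpoints and no rule joining them. If success on either marker at two-sided 0.05 counts, the false-positive rate is between 5% and 9.75%: 9.1%, 8.3% and 7.0% at correlations of 0.5, 0.7 and 0.9. These figures rest on a bivariate normal approximation and an assumed two-sided test.

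A composite, or a sequence starting with NS1, would fit both the 0.05 and the 72 events, but neither is declared. Requiring both would keep the 0.05 but not the 80% power at 72 events. Whichever was intended, a split result currently has no agreed interpretation. The rule must be fixed before unblinding, because a rule chosen with the results in view cannot be defended.

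**What to change.** State one rule, identically in Study Aims, Sample Size and the primary analysis section, that holds overall two-sided 0.05. The choice is the sponsor's, since it defines what counts as efficacy. Two suitable examples:

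- **Holm:** the smaller p-value is tested against 0.025 and, if significant, the other against 0.05. This controls the error at any correlation. It costs a stricter first threshold and 80 to 86 events per marker for 80% power.
- **Fixed sequence:** NS1 first at 0.05, since the hazard ratio is tied to NS1, and PCR at 0.05 only if NS1 is significant. It costs any PCR claim when NS1 fails.

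Under either, reword the or-phrases in the Kaplan-Meier sentence and the event count to show two separate curves and two separate tests. Restate power per marker at the level used, with each marker's assumed positivity at entry and residual at the end of follow-up. Sample Size gives 72 as the requirement but carries 138 into the formula for 220, so the event target should be reconciled in the same edit. The change is a few sentences and no extra patients are proposed.

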**Subgroup analysis**

The following sub-group analyses will be performed:

1. Comparison of primary and secondary outcomes for those with primary or secondary dengue
2. Comparison of primary and secondary outcomes for each DENV serotype
3. Comparison of primary outcome for cases with DENV viraemias >10,000 cDNA equivalents per ml at the commencement of treatment
4. Comparison of primary outcome for cases with NS1 antigenaemias >500ng/ml at the commencement of treatment
5. In subjects with at least 4 consecutive positive RT-PCR, we will determine the slope of the line representing changes in viral load over time.

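### The adjusted treatment effect comes from forward stepwise Cox selection with treatment not forced in and no covariates fixed in advance

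*Protocol*

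**What the plan says.** The protocol section on the analysis of primary endpoints restricts the analysis set: "Only study subjects who have detectable NS1 antigenaemia or viraemia (detected by PCR) at the time of study entry will be analysed". It then makes Kaplan-Meier curves the first comparison, tested "between treatment groups using log-rank test will be performed". After that comes the sentence at issue: "Adjusted treatment effect will be estimated and independent predictors will be identified using Cox regression analysis with stepwise forward variable selection procedure". The section on secondary endpoints repeats it for fever, cytokines, liver enzymes and platelets. Neither section says that treatment is always in the model, names a covariate or gives an entry rule.

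Starting marker levels are available. Observations and Investigations lists "Twice daily quantitative viral PCR from plasma for minimum 5 days" and "Twice daily assessment of Dengue NS1 levels for minimum 5 days". Subgroup analysis already uses values from the start of treatment, with cut-offs of "DENV viraemias >10,000 cDNA equivalents per ml at the commencement of treatment" and "NS1 antigenaemias >500ng/ml at the commencement of treatment". Neither level is named as an adjustment covariate.

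**The concern.** Forward selection is a tool for finding predictors. Using it to produce a randomised treatment effect raises two separate issues.

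- If treatment competes for entry like any other variable, the adjusted effect exists only in trials where treatment reaches the entry threshold. A reader then sees either no estimate or a selected, exaggerated one.
- Even if treatment is kept in, the outcome data choose the covariates separately for each endpoint. The count is 2 primary endpoints, plus 1 for fever, 6 for cytokines, 2 for liver enzymes and 1 for platelets: 2 + 1 + 6 + 2 + 1 = 12 searches. A hazard ratio changes its meaning with the covariates it is conditioned on, so up to 12 adjusted effects could rest on different, unplanned models.

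The protocol commits to this method in its own text, so this is not a detail left for a later analysis plan.

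**Working it through.** **Plan's figure.** Sample Size assumes a hazard ratio of 2 "with a power of 0.8 and type I error 0.05" and states 72 events. Freedman's formula, two-sided: (1.960 + 0.842)² × ((2 + 1)/(2 − 1))² = 7.85 × 9 = 70.6, so 71 events, which agrees with 72 to within one. (The later step from 138 to 220 needs its own reconciliation and does not bear on this point.)

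**Inputs from the protocol.** Control median 72 h; follow-up 5 days = 120 h; evaluable patients 220 × 0.8 positive at entry × 0.9 retained = 158.4, taken as 158.

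**Assumptions, not in the documents.** Exponential times; 8 candidate covariates, two of them prognostic (log hazard ratio −0.5 and −0.4 per SD, correlation 0.5); entry at Wald p < 0.05; 400 simulated trials per row.

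Treatment as an ordinary candidate (literal reading):

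| True HR | Treatment absent | Mean HR when kept | 95% CI coverage when kept |
|---|---|---|---|
| 1.0 | 94.8% | 1.59 in size, either direction | 0% |
| 1.25 | 76.5% | 1.65 | 81.9% |
| 1.5 | 46.8% | 1.77 | 92.0% |
| 2.0 | 4.0% | 2.07 | 96.9% |

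Treatment always in the model (estimated HR; coverage; rejection rate):

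| True HR | Forced in, covariates selected | Fixed two-covariate model | Unadjusted (HR; rejection) |
|---|---|---|---|
| 1.0 | 1.00; 94.8%; 5.2% | 1.00; 94.8%; 5.2% | 0.99; 5.2% |
| 1.25 | 1.26; 92.2%; 23.7% | 1.26; 92.7%; 23.3% | 1.18; 16.5% |
| 1.5 | 1.52; 92.5%; 54.2% | 1.51; 93.0%; 53.5% | 1.36; 35.7% |
| 2.0 | 2.04; 95.3%; 96.0% | 2.03; 95.8%; 96.5% | 1.69; 82.0% |

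Monte Carlo standard error for 46.8%: √(0.468 × 0.532/400) = 2.5 points; for 4.0%: √(0.04 × 0.96/400) = 1.0 point.

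**Reading the tables.**

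1. The share kept is almost the forced-in rejection rate: 100 − 46.8 = 53.2% against 54.2% at HR 1.5, and 96.0% against 96.0% at HR 2. The literal procedure therefore loses the estimate in non-significant trials. It does not raise the false-positive rate (5.2% kept at HR 1).
2. With treatment forced in, selection and fixed adjustment give practically the same result.
3. The unadjusted and adjusted estimates differ (1.69 against 2.03) although nothing is confounded. This shows how the hazard ratio depends on the covariate set.

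**Other simulations**, with 8 candidates and a single marker effect of 0.5 per SD, agree on the literal reading. Treatment was absent in about 46 to 47% of trials at HR 1.5, with mean HR 1.66 to 1.70 when kept. Across runs at HR 2 it was absent in about 1 to 5%.

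**Power.** At HR 1.65 and 0.5 per SD, fixed adjustment for the baseline marker raised power from about 0.6–0.65 (unadjusted) to about 0.72–0.75. At 0.7 per SD one run gave 0.51 to 0.68. Against forward selection with treatment in, there was no such gain. Selected against fixed was 0.820 v 0.820 and 0.775 v 0.75 in two runs at 0.5 per SD, and 0.737 v 0.740 at 0.7 per SD. The absolute level varies with the set-up, so only comparisons within a run carry weight. Where recorded, selection picked a marker of this strength in every trial.

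**The case against.** An adjusted treatment effect cannot come from a model without treatment, so the natural reading is that treatment stays and only covariates are selected. On that reading the simulations show no bias, near-nominal coverage and a type I error of 5.2%. This stands. A reader might infer that stepwise selection makes the treatment interval over-optimistic in general. The text supports that only if treatment is itself a candidate, which it permits but does not say.

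A reader might also infer that the plan forfeits power by not fixing baseline marker level. Measured against stepwise selection it does not, because a marker strong enough to matter is picked anyway. The gain is over the unadjusted comparison.

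The losses at HR 1.5 also lie below the planned effect: Sample Size designs for 2 and argues that less would matter little clinically. That is fair, and the HR 2 result must be read with them. But the protocol itself calls the assumed effect large, and a trial with a smaller true effect still needs an estimate.

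Finally, the log-rank test involves no selection, so nothing here undermines the main comparison.

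On the remedy, the analysis set admits patients positive on either marker, so some may have no measurable value of the other. Day of illness would add little, since 90% are assumed to enter on day 3.

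**Conclusion.** The point holds in a limited form. The protocol ties the adjusted treatment effect to a predictor search and does not exclude dropping treatment. On the literal reading that happens in nearly half of trials at a true HR of 1.5, with exaggeration to about 1.7 when kept, and in about 1 to 5% at HR 2. On the charitable reading the treatment estimate is sound, and the flaw is an unplanned adjustment set that can vary between endpoints. Either way, the adjusted hazard ratios are neither pre-specified nor comparable.

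The sizes rest on the assumed number and strength of covariates and on the p < 0.05 entry rule. The simulated hazard ratios are conditional on the covariates, whereas the design value of 2 comes from medians. A marginal ratio of 2 would correspond to a larger conditional one, so treatment would be dropped no more often than shown.

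**What to change.** For each time-to-event endpoint, specify one Cox model with treatment always included and covariates fixed in advance:

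- log10 baseline viral load for the PCR endpoint;
- log baseline NS1 for the NS1 endpoint;
- the baseline value of the same measure for each secondary endpoint (temperature, each cytokine, SGOT, SGPT, platelets).

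State how undetectable baseline values are handled, for example set to the detection limit with an indicator variable. Report this model beside the log-rank test. Keep any stepwise search for predictors as a separate analysis, labelled exploratory, that does not supply the treatment effect.

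The cost is wording in the two analysis sections plus the rule for undetectable values. The baseline marker and laboratory measurements are already planned, and the log-rank comparison and sample size do not change.
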